### Randomisation

The Sheffield Clinical Trials Research Unit (CTRU) and Bangor University will oversee randomisation. To ensure that assessors are blinded to group allocation, other designated members of the research team will complete randomisation. This will be via a secure remote web-based system which will allocate each participant a unique identification number. Details entered into the system will include confirmation of signed consent. Participants will then be randomly allocated to either the intervention (n = 134) or usual care (n = 134) arm of the trial. In the event of a couple both consenting to take part, the pair will be randomised as a couple and not separately, that is, to either get the intervention, or to both get usual care.

The randomisation schedule will be computer generated, stratified by site and random permuted blocks of variable size will be used to ensure enough participants are allocated evenly to each arm of the trial at each site. The participant’s GP will be notified of their involvement in the study. Participants randomised to the control arm of the trial will be informed by telephone and sent a letter confirming their allocation to keep as a record. Participants allocated to the intervention arm of the trial will first be sent a letter confirming their allocation and including contact details of the group facilitator(s). The participant will then be contacted by one of the facilitators by telephone to discuss their future involvement in the trial.

### Sample size

The primary outcome for the study is the mean SF-36 Mental Health (MH) score six months post randomisation [25]. The SF-36 MH dimension is scored on a 0 (poor) to 100 (good health) score. A previous general population survey of 3,085 Sheffield community residents aged 75 or more has demonstrated that the SF-36 can successfully be used as an outcome measure in older adults living in the community and the indications were that it was appropriate and sensitive [34]. From this general population survey, the mean SF-36 MH score was 68.3 with a standard deviation of 19.9 [34]. Differences between groups of between 5 and 10 points on the SF-36 MH score can be regarded as “clinically and socially relevant*”*[35]. The Lifestyle Matters feasibility study suggested that improvements of 7 to 14 points on the MH dimension are achievable depending on baseline functioning [36]. Assuming a standard deviation of 20 points for the SF-36 MH score at six months post randomisation, and a mean difference in MH scores between the two groups of eight or more points is clinically and practically important, then to have an 80% power of detecting this difference or more as statistically significant at the 5% (two-sided) level will require 99 participants per study arm (200 in total). However, the Lifestyle Matters intervention is a group- or facilitator led intervention. Therefore, the success of the intervention may depend on the facilitator delivering it so that the outcomes of the participants in the same group with the same facilitator may be clustered. If an average cluster size of 10 subjects per Lifestyle Matters facilitator group is assumed and an intra cluster correlation of 0.01, then the sample size must be inflated by a design effect of 1.09 to allow for this clustering giving a revised sample size estimate of 107 participants per group. Couples will be included in the trial and will count as one participant. If 20% of participants leave the study prematurely and are lost to follow-up, then it will be necessary to recruit and randomise 134 per arm (n = 268 individuals or couples (since a couple will count as one participant) in total).

### Statistical analysis

As the trial is a pragmatic parallel group randomised with a usual (control) treatment arm, data will be reported and presented according to a revised CONSORT statement [37]. Statistical analysis will be performed on an intention-to-treat-basis. All exploratory tests will be two-tailed with alpha = 0.05. Baseline demographic (for example, age, gender, number and proportion of sample who are couples) and health related quality of life data (SF-36) will be assessed for comparability between groups. The outcome data to be collected are hierarchical or multi-level in nature with individual participants nested or clustered within couples; who are nested or clustered within the Lifestyle Matters facilitation group who are then nested within a treatment group. The statistical analysis, of the outcome data, will take into account the hierarchical or clustered nature of the data by using a multi-level mixed effects linear regression model. Mixed effects models are characterised by containing both fixed and random effects. We shall assume a fixed effect for the randomised treatment group but random effects for the couple and Lifestyle Matters facilitation group. Individual participants who are not part of a couple will be treated as clusters of size one; similarly, participants randomised to the control usual care group will be treated as clusters of size one (or two if they are a couple).

To avoid bias, the independent Trial Steering Committee (TSC), the study statisticians, health economists and the research assistants collecting data at 6 and 24 months will be blinded to treatment allocation whilst the trial is ongoing. To remain blinded, assessors will not be made aware of participants’ allocation in the study and participants will be asked not to inform the assessor whether they took part in the groups when visited at 6 and 24 month follow-up. The Trial Manager, Chief Investigator, Principal Investigators, Fidelity assessment Lead, Trial Support Officer and participants will not be blinded.

#### Analysis of primary outcome

The primary analysis will compare mean SF-36 Mental Health dimension (MH) scores at six months post randomisation between the intervention group and control arms using a random-effects or multi-level mixed effects linear regression model to allow for the clustering of the outcomes within couples and Lifestyle Matters facilitation groups with baseline MH score as a covariate [38,39]. A 95% confidence interval (CI) for the mean difference SF-36 mental health dimension scores between the intervention and control arms will also be calculated. For the primary outcome, the SF-36 MH score at six months follow-up, missing data will be imputed using multiple imputations with age, gender and baseline MH scores as predictors.

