## Methods/Design

### Trial design

The study is a multi-centre pragmatic, two-arm, parallel group, individually randomised controlled trial, to investigate the implementation of a psychosocial intervention, Lifestyle Matters, which aims to promote mental wellbeing in people aged 65 years or older. Participants recruited to the study will be randomly allocated to receive either the Lifestyle Matters programme intervention in addition to usual care or to usual care only which is defined as routine access to health and social care resources. All participants will complete the same battery of outcome measures at baseline, 6 months and 24 months to ascertain the benefits that might be derived from participation immediately after cessation of involvement and over time. The trial will be delivered at two study sites, one city in the North of England and in North Wales. The trial will adhere to the Medical Research Council (MRC) framework for the evaluation of complex interventions [20]. A CONSORT-style flow diagram is provided in Figure 1[21]. The study has been approved by the South Yorkshire Research Ethics Committee, the National Institute for Social Care and Health Research (NISCHR) Permissions Co-ordinating Unit in Wales, Sheffield Health and Social Care NHS Foundation Trust, NHS Sheffield, Sheffield Teaching Hospitals NHS Foundation Trust, Betsi Cadwalador University Health Board (BCUHB) and Sheffield City Council. The trial is registered with Current Controlled Trials, reference number ISRCTN67209155.

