### Participant recruitment

A number of geographical areas will be identified in a city in the North of England and in North Wales for recruitment and subsequent intervention delivery. Recruitment and intervention delivery will be in three cycles, each cycle being cited in a community location where the recruited participants reside. The intention is to recruit enough participants to hold two groups of 6 to 18 participants in each location. Older adults aged 65 years and over who are living in their own home or with others will be identified through targeted General Practitioner (GP) mail-outs; signposting by health and social care staff who are likely to come into contact with older people in their work; community based voluntary sector organisations for older people and through community engagement and advertisements. A range of marketing materials will be used to advertise the study and will be made available in English and Welsh.

The main risk to recruitment is the GP mail-outs where there is little control over who responds, leading to two issues. Firstly, those who have self-identified a need or are already confident enough to attend an intervention like Lifestyle Matters and, secondly, attracting only individuals who are already active in their personal life and within their community. To reduce these risks, advice will be sought from local authorities and primary care on potential areas at both sites which currently have limited or less access to community services and other research-based opportunities. It is also anticipated that regardless of individual circumstances, those who register an interest in the study will have a personal reason for doing so.

It is anticipated that the number and availability of GPs will differ in each geographical location and may introduce risk to recruitment. This will pose a greater challenge in North Wales, which predominantly consists of smaller, rural community GPs. In the North of England site, which is a large city, there is anticipated to be enough GP surgeries to conduct recruitment for two groups in each cycle. Assistance with recruitment will, therefore, be sought from the Primary Care Research Network (PCRN) in England and the National NISCHR in North Wales both of which regularly work with research active GPs.

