#### Analysis of secondary outcomes

Secondary outcomes, such as the other dimensions of the SF-36, EQ-5D-3L, BRS, GSE, de Jong Gierveld Loneliness Scale at six months’ follow-up, will be compared between the intervention and control arm using a multi-level mixed effects linear regression model with baseline score as a covariate. A 95% CI for the mean difference in this parameter between the treatment groups will also be calculated. Participants will be followed up at 24 months post randomisation. Mean SF-36 (MH), other SF-36 dimensions, BRS, GSE, PHQ-9, EQ-5D-3L, de Jong Gierveld Loneliness Scale dimension scores at 24 months’ follow-up will be compared again using multi-level mixed effects linear regression model with baseline score as a covariate. A 95% CI for the mean difference in this parameter between the treatment groups will also be calculated.

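### Site, the only stratification factor, is absent from the stated primary and secondary models, so any site difference left after baseline adjustment makes the standard error somewhat too large

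*Protocol article*

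**What the plan says.** All references are to the protocol article.

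- **Trial design:** "The trial will be delivered at two study sites, one city in the North of England and in North Wales".
- **Randomisation:** "The randomisation schedule will be computer generated, stratified by site and random permuted blocks of variable size will be used". No other stratification factor is named.
- **Statistical analysis:** "We shall assume a fixed effect for the randomised treatment group but random effects for the couple and Lifestyle Matters facilitation group". On the control arm, "participants randomised to the control usual care group will be treated as clusters of size one", or of size two for a couple.
- **Analysis of primary outcome:** the model is a mixed linear regression "to allow for the clustering of the outcomes within couples and Lifestyle Matters facilitation groups with baseline MH score as a covariate". Missing six-month scores are multiply imputed from age, gender and baseline Mental Health (MH) score.
- **Analysis of secondary outcomes:** outcomes "will be compared between the intervention and control arm using a multi-level mixed effects linear regression model with baseline score as a covariate", with the same form repeated at 24 months.
- **Participant recruitment:** "Recruitment and intervention delivery will be in three cycles, each cycle being cited in a community location where the recruited participants reside", with two groups intended per location.

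Site therefore appears in the randomisation but in none of the stated analysis or imputation models.

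**The concern.** An analysis should normally reflect the restrictions placed on the randomisation. Here the article lists fixed effects, random effects and covariate, and the one design factor is not among them.

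The partially nested layout makes the omission matter more than it would in a trial with independent outcomes. Every facilitation group sits wholly within one site. If mean MH differs between the sites after baseline adjustment, the group means differ for that reason alone, and the model attributes the spread to facilitation. It then charges that spread to the treatment effect over roughly a dozen groups rather than over a hundred or so individuals. In the control arm there is no group term, so the same difference goes into the residual.

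Stratification has already balanced site out of the treatment comparison, so the reported SE includes variation that the estimate does not contain. At stake are some precision and a clean reading of the facilitator-group ICC, on which the sample size inflation rests. The validity of the estimate is not at stake.

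**Working it through.** **1. The plan's own figures.** Inputs from the Sample size section: SD 20, difference 8, two-sided 5%, 80% power, cluster size 10, ICC 0.01, 20% loss.
- n per arm = 2 × (1.96 + 0.8416)² × 20² / 8² = 98.1, rounded up to 99.
- Design effect = 1 + (10 − 1) × 0.01 = 1.09, and 99 × 1.09 = 107.9 (the article gives 107).
- 107 / 0.8 = 133.75, so 134 per arm.

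The stated sample size reproduces. It takes no credit for baseline adjustment.

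**2. Layout.** 2 sites × 3 cycles × 2 groups per location = 12 groups. With 9 analysed per group that is 108 in the intervention arm, set against 108 controls and close to the plan's 107.

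**3. Assumptions not in the documents.** Baseline-outcome correlation 0.6. Site gap of 5 or 8 points, in two forms: (a) stable, already present at baseline; (b) arising only after baseline. ICC 0.01 is applied to the adjusted variance.

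**4. Residual gap D after baseline adjustment.**
- (a) The baseline covariate removes about 60% of a stable gap: 5 × 0.4 = 2.0 and 8 × 0.4 = 3.2.
- (b) Nothing is removed: 5 and 8.

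**5. Hand calculation.** Adjusted variance = 400 × (1 − 0.36) = 256; group part 2.56, individual part 253.44.
- Variance of the arm difference with site modelled = 2.56/12 + 253.44/108 + 256/108 = 0.213 + 2.347 + 2.370 = 4.930, so SE = 2.220.
- Omitting site adds about (D/2)²/12, because half the groups lie D/2 above and half D/2 below the overall mean.

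| Case | D | Added variance | SE ratio |
|---|---|---|---|
| Stable 5 | 2.0 | 0.083 | √(5.014/4.930) = 1.008 |
| Stable 8 | 3.2 | 0.213 | √(5.144/4.930) = 1.021 |
| New 5 | 5 | 0.521 | √(5.451/4.930) = 1.051 |
| New 8 | 8 | 1.333 | √(6.264/4.930) = 1.127 |

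**6. Simulation of the planned model by REML** (same layout, correlation 0.6, group variance 4, 800 runs per scenario).
- Stable 5: mean SE 2.302 without site, 2.292 with (+0.4%); power 93.4% against 93.5%.
- Stable 8: 2.331 against 2.294 (+1.6%); power 93.9% against 94.0%.
- New 5: +4.2%. New 8: +11.4%.

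Hand calculation and simulation together give about 0.4 to 2% for a stable gap and about 4 to 13% for a new one.

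**7. The mechanism.** A second simulation (600 runs, group variance 2.56) with D = 8 remaining after adjustment gave:

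| | Without site | With site |
|---|---|---|
| Mean estimated group variance | 21.3 | 7.2 |
| Mean model SE | 2.56 | 2.29 |
| Actual SD of the estimate | 2.26 | 2.26 |
| Coverage of 95% CI | 97.3% | 95.3% |

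The estimate is equally variable either way; only its reported SE changes.

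**8. Power,** from Φ(8/SE − 1.96). At correlation 0.6 it is 95% with site. Without site and with D = 8, SE = √6.264 = 2.503 and power is Φ(1.24) = 89%. A slightly stricter calculation takes the between-group variance on 11 degrees of freedom and adds the control-arm share of the site variance. It gives 88% at D = 8 and 84% at D = 10.

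**The case against.** **The full analysis plan may include site.** The oversight section of the article refers to a statistical analysis plan, and naming the baseline score as a covariate does not exclude others. This is fair, and that plan may already settle the matter. Still, the article goes beyond a general statement: it lists the fixed effect, the random effects and the covariate, for primary and secondary outcomes alike. As written, the model omits the design factor.

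**The loss is small.** This largely stands. A stable difference between sites shows at baseline too, and the planned covariate removes most of it. The larger inflation needs sites that are alike at baseline and then diverge by 5 to 8 points in six months, where 8 points is the whole target effect. Nothing in the documents supports a divergence of that size.

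**There is no validity problem.** This also stands. The estimate is unbiased and the error is conservative, so no false claim of benefit follows.

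**Stronger readings that a reader might infer.**
- *That the trial loses its planned power.* At correlation 0.6 power stays above 80% even with a 10-point residual gap. It falls below 80% only under assumptions such as a baseline score that carries no information: at correlation 0 the stricter calculation gives 82% with site, and 79% and 75% without it at residual gaps of 5 and 8. Such figures leave out the benefit of the baseline covariate that the plan specifies.
- *That the design also balances recruitment location, so location must be in the model.* The Randomisation section stratifies by site only. Sequential cycles with blocked allocation may balance location roughly, but that is not a stratification, and the documents give no location ICC.

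**Conclusion.** The point holds as a modest loss of efficiency and of clarity. The stated primary and secondary models leave out the only stratification factor. Because of the nesting, a residual site difference is counted as facilitation-group variance, which enlarges the SE, makes the confidence interval conservative and blurs the group ICC.

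The size rests on two quantities that the documents do not give, the site difference and the baseline-outcome correlation, and on a layout of 12 groups of 9. If no site difference survives baseline adjustment, the loss is nil. The documents do not support a claim of bias, of invalid inference or of a power shortfall. The correction is worth making because it costs almost nothing and should be fixed before allocation is unblinded; added later, it could look driven by the data.

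**What to change.** - Add site as a fixed effect (two levels) to the primary model and to every secondary model at 6 and 24 months, keeping baseline score and the couple and facilitation-group random effects.
- Add site to the predictors in the multiple imputation of the six-month MH score.
- Optionally, name a sensitivity analysis with recruitment location (site × cycle, six levels) as a fixed effect in place of site, stating that location was not a stratification factor. This uses five degrees of freedom instead of one.

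The main change is a line of wording and one degree of freedom per model. Sample size, randomisation and trial conduct are unaffected. If the full statistical analysis plan already contains site, it is enough to confirm that.

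### The imputation model for the primary outcome leaves out randomised arm, which pulls the treatment effect towards zero by about the missing fraction (8 points becomes about 6.4 at 20% missing)

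*Protocol article*

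**What the plan says.** The protocol's section Analysis of primary outcome fixes the handling of missing six-month MH scores: "missing data will be imputed using multiple imputations with age, gender and baseline MH scores as predictors". Three predictors are named: age, gender and baseline MH. Randomised arm, couple, facilitation group and site are not among them. No other section mentions arm in the imputation or imputation by arm.

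The analysis model is richer. Under Statistical analysis the protocol states: "We shall assume a fixed effect for the randomised treatment group but random effects for the couple and Lifestyle Matters facilitation group". The primary comparison is fitted "with baseline MH score as a covariate".

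The planning figures are under Sample size. The target is that "a mean difference in MH scores between the two groups of eight or more points is clinically and practically important", with a standard deviation of 20. The loss allowance reads "If 20% of participants leave the study prematurely and are lost to follow-up".

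**The concern.** An imputation model should contain every variable in the analysis model, above all the one whose effect is being estimated. Here it does not. With a single model pooled over both arms, two participants with the same age, gender and baseline MH have their missing scores drawn from the same distribution, whichever arm they are in. That distribution is a blend of the two arms. The imputed part of the sample therefore shows no expected treatment difference, and it dilutes the difference among those observed.

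Three things are at stake:

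- The primary estimate and its confidence interval are shifted towards no effect.
- The standard error from Rubin's rules is too large for this estimator, so power is lost a second time.
- If missingness depends only on arm and baseline MH, a complete-case analysis adjusted for baseline MH is unbiased. The stated imputation would then make the primary analysis worse than not imputing at all.

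**Working it through.** **Inputs from the protocol.** Difference 8, SD 20, 80% power, two-sided 5%, cluster size 10, intra-cluster correlation 0.01, 20% loss (Sample size); 134 per arm (Randomisation); predictor list and baseline covariate (Analysis of primary outcome).

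**1. The protocol's own sample size is reproduced.**
- n per arm = 2 × [20 × (1.960 + 0.842) / 8]² = 98.1, rounded up to 99.
- Design effect = 1 + (10 − 1) × 0.01 = 1.09, and 98.1 × 1.09 = 106.9, rounded to 107.
- 107 / 0.80 = 133.75, rounded up to 134.

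**2. Expected attenuation.** Let the true difference be δ, the missing fractions m_T and m_C, and p the intervention share of those observed. Relative to the control mean, arm-free imputed values have mean pδ in both arms.
- Intervention mean: (1 − m_T)δ + m_T·pδ. Control mean: m_C·pδ.
- Expected estimate: δ[1 − m_T(1 − p) − m_C·p].
- With equal loss m, p = 0.5 and this becomes δ(1 − m).

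| Missing (intervention / control) | Expected estimate when the truth is 8 |
|---|---|
| 10% / 10% | 7.2 |
| 20% / 20% | 6.4 |
| 30% / 30% | 5.6 |
| 30% / 10% | 6.3 |

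The result does not depend on the correlation between baseline and six-month MH.

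**3. Simulation.** 134 per arm, 1,500 trials per row, 20 proper normal-regression imputations, Rubin's rules, linear model on arm and baseline MH, 20% missing, true difference 8. The protocol gives no baseline-to-outcome correlation r, so r is an assumption and a range is shown.

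| Scenario | Arm omitted: estimate, power | Arm included: estimate, power |
|---|---|---|
| r = 0 | 6.35, 67% | 8.03, 84% |
| r = 0.5 | 6.38, 82% | 8.08, 92% |
| r = 0.7 | 6.44, 95% | 8.02, 98% |
| r = 0.5, missingness depends on baseline MH | 6.25, 80% | 7.99, 91% |

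With arm omitted and r = 0.5, 10% missing gave 7.18 and 30% gave 5.50. These rows ignore clustering. Runs with an intra-cluster correlation of 0.01 in groups of 10 gave 6.4 to 6.5, so clustering at the planned level does not change the picture. For a smaller true effect of 5 at r = 0.6, power was 44% with arm omitted against 62% with it included.

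**4. Standard error.** At r = 0.5 with arm omitted, the Monte Carlo error of the mean was 0.0486. The true spread of the estimate is therefore 0.0486 × √1500 = 1.88, while the average Rubin standard error was 2.37. With arm included the figures are 0.0600 × √1500 = 2.32 and 2.38, which agree.

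**5. No true effect (r = 0.5).** The mean estimate was −0.02 with arm omitted. The type I error was 2.4%, against 4.6% with arm included.

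**The case against.** The strongest reply is that the sentence does not say that these are the sole predictors or that the two arms are pooled. The same three predictors used within each arm would satisfy the wording and cause no attenuation. This is a condensed article, and a statistical analysis plan not shown here may say more. That is fair as far as it goes. But the protocol chose to name the predictors, the list reads as complete, and a plan that followed it literally would reproduce the bias.

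Other points carry some weight:

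- **20% is a planning allowance, not an observed rate.** The attenuation is conditional on it, which is why a range is given.
- **Power may still reach the planned 80%.** With r of 0.5 or more and loss unrelated to baseline, arm-free imputation kept power at 82% or higher. The 67% figure needs a baseline score that predicts nothing. The loss compared with including arm remains: about 9 points at r = 0.5.
- **The direction is conservative.** The error cannot manufacture a benefit. It can hide or understate one, in a trial meant to inform commissioning.
- **Site is not in the stated analysis model.** It is a stratification factor, so leaving it out of the imputation is not an incompatibility with that model.
- **The clustering terms matter less.** Facilitation groups exist only in the intervention arm and the planned intra-cluster correlation is 0.01. No material harm from omitting group or couple has been shown.
- **Extra auxiliary variables are a refinement.** Participants lost by six months will often lack 24-month MH as well.

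**Conclusion.** The concern holds. As worded, the imputation model omits the variable whose effect the trial estimates. With one model pooled over arms, the primary estimate is biased towards zero by about the missing fraction. At the protocol's 20% loss and 8-point target, the expected estimate is 6.4 (simulated 6.25 to 6.44). An effect exactly at the stated importance threshold would on average be reported 1.6 points below it.

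The size of the bias rests on the missing fraction and on pooling over arms. It does not rest on the baseline correlation. The power figures do rest on that correlation, which the protocol does not give. Because the bias is in the primary analysis, predictable and free to remove, it should be corrected before the analysis is run.

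**What to change.** Replace the predictor list in Analysis of primary outcome. Suggested wording: *Missing six-month MH scores will be multiply imputed separately within each randomised arm, using age, gender and baseline MH score, with the imputation allowing for couples and, in the intervention arm, facilitation groups.* Adding arm as a predictor in a single imputation model would also remove the bias; in simulation the estimate returned to 8.0 to 8.1.

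Optional additions that may improve precision or make the missing-at-random assumption more plausible are site, baseline PHQ-9, the other baseline SF-36 dimensions, and 24-month MH where available. A complete-case analysis with the baseline covariate is a useful check alongside. If a statistical analysis plan exists, it should carry the same wording.

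The cost is one sentence. No new data are collected and no further participants are needed.
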